### 4.3 Randomization:

Computer generated randomization lists will be created for each of the 4 study sites by a member of the project who will not be directly involved in the conduct of the study. Sealed copies of the original randomization lists and documentation of the procedure used to generate the lists will be stored in the project administrative offices in Kampala. Prior to the onset of the study, sealed copies of the randomization lists will be distributed to the study nurse responsible for treatment allocation.

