## 5.3 Selection criteria

On day 0, patients with symptoms suggestive of malaria and a positive screening thick blood smear will be assessed for the following selection criteria:

1. Not previously enrolled in this study
2. Age 1 – 10 years
3. Weight > 10 kg
4. Fever (> 37.5ºC axillary) or history of fever in the previous 24 hours
5. Absence of any history of serious side effects to study medications
6. No evidence of a concomitant febrile illness in addition to malaria
7. Provision of informed consent (appendix 5) and ability to participate in 28-day follow-up (patient has easy access to health unit)
8. No danger signs or evidence of severe malaria defined as:

- Unarousable coma (if after convulsion, > 30 min)
- Repeated convulsions (> 2 within 24 h)
- Recent convulsions (1-2 within 24 h)
- Altered consciousness (confusion, delirium, psychosis, coma)
- Lethargy
- Unable to drink or breast feed
- Vomiting everything
- Unable to stand/sit due to weakness
- Severe anaemia (Hb < 5.0 g/dL)
- Respiratory distress (laboured breathing at rest)
- Jaundice (yellow coloring of eyes)

Patients fulfilling these criteria will be assigned a study number and will be referred to the laboratory. A fingerprick blood sample will be obtained to prepare thick and thin blood smears, and for measurement of haemoglobin. After going to the laboratory, the subjects will be referred to the study nurse for treatment allocation and treatment with the study medications. Patients must also meet the following criteria:

1. Absence of repeated vomiting of study medications on day 0

Results of the Giemsa-stained thick and thin blood smears obtained on day 0 will not be available until after the patients have been treated and discharged from the clinic. Patients will return to the clinic on day 1 and will be excluded from the study if the following inclusion criteria are not met:

1. *P. falciparum* mono-infection
2. Parasite density > 2000/ul and < 200,000/ul

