## 6.2 Treatment group assignment

Patients will be randomly assigned to one of the two treatment groups (AQ+AS or coartemether). Randomization will be done according to a pre-determined randomization list. Treatment allocation and administration of medications will be performed by the study nurse.

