## 6.3 Treatment allocation

To allocate subjects to the appropriate treatment group, the study nurse will select the next available treatment number and corresponding study regimen. The study nurse will record the data and time of treatment assignment and the patient's study number.

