## 6.5 Treatment administration and blinding

Study medications will be administered according to weight-based guidelines (Appendix 6). Study medications will not be identical in appearance or taste, but the number of doses received will be similar (2 different medicines in the morning, 1 medicine in the evening) for patients in both treatment groups. Patients will not be informed of their treatment regimen, and all study staff involved in the assessment of patient outcomes, including the study clinicians (responsible for clinical assessment and measurement of temperature) and laboratory technicians (responsible for reading thick blood smears and determining parasite density) will be blinded to the treatment group assignments

Both the morning and evening doses of the study medication will be administered in the clinic. Study medications given to young children will be crushed, mixed with water, and administered as slurry. Study medications administered to older children and adults will be given as tablets or fractions of tablets to be taken orally with a glass of water. The study nurse will directly observe consumption of study medications. Patients will be observed for 30 minutes to ensure that the medications are not vomited. Any patient who vomits the medication within 30 minutes of administration will be retreated with a second dose. Any patient who vomits repeatedly (> 3 times) will be treated with/referred for treatment with parenteral quinine and recoded as having complicated malaria.

On day 0, the first dose of study medication will be administered before 11.00 a.m. and the second dose will be administered in the evening, approximately 8 hours later. On days 1 and 2, the first dose of study medication will be administered before 9.00 a.m. and the second dose will be administered in the evening, approximately 12 hours later.

Study participants will be free to either wait at the clinic or go home and return in the evening for the evening dose of study medications. Participants who opt to wait at the clinic shall wait in a specially designated waiting area. Participants will be reimbursed for transport to and from the clinic and for lunch (those who opt to wait at the clinic for the evening dose of medications). Home visitors shall actively follow patients who do not come for scheduled appointments.

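### The nurse who allocates treatment holds the randomisation list, and the protocol describes no per-patient concealment of the assignments still to come

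*Protocol*

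**What the plan says.** Generation of the sequence is independent. Section 4.3 says "Computer generated randomization lists will be created for each of the 4 study sites by a member of the project", and that this person has no direct part in running the study. Sealed copies of the original lists, with documentation of how they were generated, are stored in Kampala.

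The handover to the site is in the same section: "sealed copies of the randomization lists will be distributed to the study nurse responsible for treatment allocation". This happens before the study starts.

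Sections 6.2 and 6.3 describe the use of the list:

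- "Randomization will be done according to a pre-determined randomization list" (6.2).
- "Treatment allocation and administration of medications will be performed by the study nurse" (6.2).
- At each allocation, "the study nurse will select the next available treatment number and corresponding study regimen" (6.3).
- "The study nurse will record the data and time of treatment assignment and the patient's study number" (6.3; 'data' is evidently meant as 'date').

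On the order of steps, section 5.3 says of children who meet the day-0 criteria: "Patients fulfilling these criteria will be assigned a study number and will be referred to the laboratory". The nurse comes after the laboratory, and Appendix 1 shows the treatment number being assigned at that last step.

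**The concern.** A good sequence protects a randomised comparison only if those handling patients cannot see what comes next. A seal on a whole list works until the list is first opened. From then on, whoever holds it can read ahead unless something else hides the later entries, and the protocol names nothing else.

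What is at stake is comparability of the arms within a site. If the next regimen is known while several children wait, the choice of which child takes which number can depend on how ill each child looks. If the next regimen is passed to the clinicians, their screening judgements can depend on it. Some selection criteria leave room for judgement, such as evidence of another febrile illness or ability to complete 28 days of follow-up. The results are meant to inform national drug policy (2.3), so a weakness this easy to close is worth closing.

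**Working it through.** The point rests on reading the sections together. The only arithmetic is one subtraction.

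**1. What is handed over.** Section 4.3 speaks of sealed copies of the lists. The object sealed is the list. The section does not say whether single entries are also covered, who opens the copies, when they are opened, or whether each nurse receives only the list for that nurse's own site.

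**2. How it is used.** Section 6.2 bases assignment on the predetermined list, and 6.3 has the nurse take the next treatment number together with its regimen. To learn the first regimen, the nurse must have opened what was sealed. On the plain reading, the later lines are then legible.

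**3. How much is exposed.** Section 9.1 plans 400 patients per site. The length of the list is not stated. Assuming one entry per planned patient, 400 − 1 = 399 assignments per site could be read after the first allocation. This is an upper bound and depends on the whole-list reading in steps 1 and 2. If entries are individually covered, the exposure falls away.

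**4. Whether another safeguard hides the next assignment.** None of 4.3, 6.2, 6.3 or 6.5 describes an envelope per patient, a coded pre-packed course, or assignment by telephone or from a central office. The record of date, time and study number in 6.3 is made at assignment. It allows later checking but does not prevent foresight.

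**5. Which routes the order of steps already closes.** Laboratory technicians read the screening smear (5.2). A clinician sees the child and the screening form is completed (Appendix 1). Clinicians seek consent (12.4) and are to be blinded (6.5). The study number is given before the laboratory visit, and the nurse comes last (5.3, 6.1, Appendix 1). The nurse has no screening or consent task and so cannot directly decide who enters.

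**6. Which routes stay open.**

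- *Re-ordering.* Study number and treatment number are separate. Nothing says that treatment numbers must be issued in study-number order. A nurse who can see the next entries could decide which of several waiting children takes which one.
- *Disclosure.* Nothing prevents the nurse from telling a clinician which arm comes next before another child is screened.

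**7. Whether the log would reveal re-ordering.** Partly. Comparing study-number order with treatment-number order would show departures. However, children may return from the laboratory at different times, so some departures would be innocent, and no rule separates the two. Nor does the protocol plan to reconcile the log with the Kampala list.

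**The case against.** The strongest reply is that the protocol does not say the nurse reads the whole list. It is silent on the form of the seal, and taking the next available number also fits entries that are covered one by one. That stands: the point is a plain reading, not a stated fact. But if individual covering was intended, 4.3 has to say so, and the amendment is the same.

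The second reply is separation of roles: the nurse neither screens nor consents, the clinicians who do are meant to be blinded, and study numbers are fixed beforehand. This also stands, and it limits the point to the two indirect routes above. A reader might infer that the nurse can choose who is enrolled according to arm. The documents do not support this, since every enrolment decision up to the study number belongs to others.

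A reader might also link the list to the exclusion for repeated vomiting on day 0, because the nurse watches the doses being taken ("The study nurse will directly observe consumption of study medications"), or to the differing appearance of the tablets. Neither belongs here. Both concern the arm a child is already receiving, which the nurse knows by design in this single-blind trial. Hiding future assignments would change neither.

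**Conclusion.** The point holds as a weakness in a procedure that the protocol itself fixes, and it is not a detail left to an analysis plan. The allocating nurse holds the list, and no per-patient concealment is described. On the plain reading, up to 399 of 400 assignments per site become visible after the first. That figure assumes a whole-list seal and a list of 400 entries.

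Its practical reach is limited to re-ordering waiting children and disclosing the next arm to clinicians, with only a date-and-time log as a check. Nothing in the documents suggests that either will happen.

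A reader might want to express this as a shift in the difference between arms. The protocol gives neither a rate of re-ordering nor a risk gap between re-ordered children, so any such figure would be invented. A reader might also infer that resulting bias would be beyond repair in analysis. That is too absolute: imbalance in recorded baseline factors, such as age and parasite density, could be examined and adjusted for, while imbalance in unrecorded factors could not.

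This is a cheap improvement that should be made. It is not a defect that invalidates the design.

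**What to change.** Amend 4.3 and 6.3 as follows:

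- Keep the full lists only in Kampala, where sealed copies are already stored. Send no list to a site.
- Supply each site with sequentially numbered, opaque, individually sealed assignments, or with pre-packed numbered courses.
- Open them one at a time, in study-number order, and only after eligibility, consent and study number are recorded. Because a child can still be excluded at the laboratory step (Appendix 1), or may be delayed there, require a recorded reason whenever a study number is passed over.
- Keep the existing record of date, time and study number, and reconcile it with the Kampala master list.

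The cost is stationery, some preparation time from the person who already generates the lists, and the reconciliation. Opening in study-number order may occasionally make a child wait. Independent list generation, study number before allocation, and the log are already in place. Sample size and clinical care are unaffected.

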# 5.0 PARTICIPANT SELECTION AND ENROLLMENT

## 5.1 Study site

The study will be conducted at 4 of the Uganda Malaria Surveillance Project (UMSP) sentinel sites that were originally established in 1998 by the Ugandan Ministry of Health (MoH) in collaboration with the East African Network for Monitoring Antimalarial Treatment (EANMAT).

Table 2. UMSP sentinel sites

| **District** | **Health center** | **Region type** | **Catchment population** | **Transmission** |
| --- | --- | --- | --- | --- |
| Tororo | Nagongera | Rural | 26,010 | Holoendemic |
| Kanungu | Kihihi | Rural | 14,000 | Mesoendemic |
| Mubende | Kasambya | Rural | 40,000 | Hyperendemic |
| Arua | Chilio | Rural | 15,685 | Holoendemic |

## 5.2 Recruitment and screening process (Appendix 1)

Study subjects will be recruited from the OPD (outpatient department) of the sentinel health centre. Patients who present with symptoms suggestive of malaria (fever or history of recent fever) will be referred to the outpatient laboratory for a screening thick blood smear (using standard Giemsa staining). Thick blood slides will be read and counted by the laboratory technicians. The parasite density of positive screening thick blood smears will be estimated by the laboratory technicians by counting the number of asexual parasites per 200 leukocytes, assuming a leukocyte count of 8,000/l. All patients who have a positive screening thick smear with a parasite density of > 2000/ul (> 50 parasites per 200 leucocytes) and < 200,000/ul (< 5000 parasites per 200 leucocytes) will be referred to the study clinic for further evaluation. If the patient satisfies the selection criteria, they will be enrolled in the study. All patients who do not satisfy the selection criteria and are excluded from study enrolment will be referred back to the outpatient department for appropriate care.

## 5.3 Selection criteria

On day 0, patients with symptoms suggestive of malaria and a positive screening thick blood smear will be assessed for the following selection criteria:

1. Not previously enrolled in this study
2. Age 1 – 10 years
3. Weight > 10 kg
4. Fever (> 37.5ºC axillary) or history of fever in the previous 24 hours
5. Absence of any history of serious side effects to study medications
6. No evidence of a concomitant febrile illness in addition to malaria
7. Provision of informed consent (appendix 5) and ability to participate in 28-day follow-up (patient has easy access to health unit)
8. No danger signs or evidence of severe malaria defined as:

- Unarousable coma (if after convulsion, > 30 min)
- Repeated convulsions (> 2 within 24 h)
- Recent convulsions (1-2 within 24 h)
- Altered consciousness (confusion, delirium, psychosis, coma)
- Lethargy
- Unable to drink or breast feed
- Vomiting everything
- Unable to stand/sit due to weakness
- Severe anaemia (Hb < 5.0 g/dL)
- Respiratory distress (laboured breathing at rest)
- Jaundice (yellow coloring of eyes)

Patients fulfilling these criteria will be assigned a study number and will be referred to the laboratory. A fingerprick blood sample will be obtained to prepare thick and thin blood smears, and for measurement of haemoglobin. After going to the laboratory, the subjects will be referred to the study nurse for treatment allocation and treatment with the study medications. Patients must also meet the following criteria:

1. Absence of repeated vomiting of study medications on day 0

Results of the Giemsa-stained thick and thin blood smears obtained on day 0 will not be available until after the patients have been treated and discharged from the clinic. Patients will return to the clinic on day 1 and will be excluded from the study if the following inclusion criteria are not met:

1. *P. falciparum* mono-infection
2. Parasite density > 2000/ul and < 200,000/ul

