# 9.0 STATISTICAL CONSIDERATIONS

## 9.1 Sample size calculations

The sample size calculations will be made for the study based on the estimated efficacy of the combination regimens to be studied in the given regions. For the purposes of sample size calculation, the risk of clinical rescue therapy will be the primary outcome. If the null hypothesis states that there is no difference in clinical outcome between the treatment groups, we plan to test the alternative hypothesis that treatment with an alternative combination regimen will decrease the likelihood of clinical failure at 28 days of follow-up. The risk of clinical rescue therapy with AQ+AS is estimated to be 40-50% based on previous data (UMSP, unpublished data). We plan to enroll 200 patients in each treatment arm at all of the study sites (400 patients per site, 1600 patients total). Based on an α = 0.05 (two-sided) and a power of 80%, allowing for 10% loss to follow-up, we will have the ability to detect a risk difference of approximately 15% between the two treatment groups.

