# APPENDIX 7. CLASSIFICATION OF RESPONSE TO TREATMENT

**Early Treatment Failure (ETF)**

| **ETF**   - Development of danger signs or severe malaria on Day 1, Day 2 or Day 3 in the presence of parasitemia - Parasitaemia on day 2 higher than Day 0 count irrespective of axillary temperature. - Parasitaemia on Day 3 with axillary temperature > 37.5 0C - Parasitaemia on Day 3 > 25% of count on Day 0. - Severe AE requiring change in treatment Days 0 - 2 |
| --- |

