****(Grade on scale of 0-4: normal = 0; mild abnormality = 1; moderate = 2; severe = 3, life-threatening = 4)***

***† Any haemoglobin <*** 5g/dl measured after Day 0 is a serious AE. Notify Kampala core facility immediately of all serious adverse events.

| **RECORD OF ADDITIONAL MEDICATION GIVEN DURING STUDY** | | | | |
| --- | --- | --- | --- | --- |
| **Medication (a)** | **Indication (b)** | **Dose (c)** | **Duration (d)** | **Date started (e)** |
| **60.** |  |  |  |  |
| **61.** |  |  |  |  |
| **62.** |  |  |  |  |
| **63.** |  |  |  |  |
| **64.** |  |  |  |  |
| **65.** |  |  |  |  |
| 66. |  |  |  |  |
| **67.** |  |  |  |  |
| **68.** |  |  |  |  |
| **69.** |  |  |  |  |
| **70.** |  |  |  |  |

| **UMSP clinical record form (4):** | | | |
| --- | --- | --- | --- |
| **Patient**  **Initials:** | **1. Study Number: U**|___|___|___|___|___| | **2. Day 0 Date:** |___|___|/|___|___|/|___|___|  ***day month year*** | **3. Treatment Number:** |___|___|___| |

| complete efficacy outcome | |
| --- | --- |
|  ETF     LCF   LPF   ACPR     N/A (Tick appropriate Incomplete Efficacy Outcome **)** | If failed, **STUDY DAY** of clinical failure (0-28) __________  **Reason for ClinicalFailure:**   Severe malaria/danger signs with parasitemia Days 0-3  Specify criteria _________   Severe AE requiring change in treatment Days 0-2  Specify criteria _____________   Day 2 parasite count > Day 0 count   Parasitemia on Day 3 with temperature > 37. 5   Day 3 parasite count > 25% Day 0 count   Severe malaria with parasitemia Days 4-28  Specify criteria __________________   Parasitemia on Days 4-28 with temperature > 37. 5 OR History of fever in past 24 hours. |

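### Repeated vomiting of study drug on Day 0 is a selection criterion judged after allocation and dosing, and inconsistent coding may drop the event from both the efficacy and the tolerability comparisons

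*Protocol*

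**What the plan says.** Section 5.3 sends eligible patients to the study nurse for allocation and the first dose, and then adds one more requirement: "Absence of repeated vomiting of study medications on day 0". Section 1.0 has the same item as criterion 9. The screening form (Appendix 2, item 14) has it too, with the word persistent in place of repeated, and instructs that a failing answer excludes the patient.

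Section 6.5 covers the same event without limiting it to Day 0: "Any patient who vomits repeatedly (> 3 times) will be treated with/referred for treatment with parenteral quinine and recoded as having complicated malaria".

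The outcome definitions offer a further route. Appendix 7 lists, as early treatment failure (ETF), a severe adverse event that forces a change of treatment on Days 0 to 2, and clinical record form (4) in Appendix 12 repeats this. Danger signs are a separate ETF ground. Appendix 7 gives it as "Development of danger signs or severe malaria on Day 1, Day 2 or Day 3 in the presence of parasitemia", whereas the form has "Severe malaria/danger signs with parasitemia Days 0-3".

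Section 4.2.1 builds the primary outcome from ETF plus late clinical failure, and treats every ETF as a true failure. Section 9.2 restricts efficacy to a per-protocol analysis of patients who have an outcome.

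**The concern.** Whether a child vomits the assigned drug is a result of the assignment. Using it to decide who belongs in the trial makes the analysed groups depend on what they were given. The other criteria checked late, species and parasite density, are different: their blood sample is taken before dosing, so treatment cannot affect them.

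The person who observes the vomiting is not blinded. The nurse holds the list (Section 4.3), allocates and gives the drug (Section 6.2) and watches it being taken (Section 6.5), and the medicines differ in look and taste. Three different terms (repeated, persistent, more than three times) leave room for judgement.

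At stake are a count in the primary outcome and a direct measure of tolerability, which is part of the trial's title and aim.

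**Working it through.** **1. The plan's own figure.** Inputs from Section 9.1: "Based on an α = 0.05 (two-sided) and a power of 80%, allowing for 10% loss to follow-up"; "The risk of clinical rescue therapy with AQ+AS is estimated to be 40-50% based on previous data"; "We plan to enroll 200 patients in each treatment arm at all of the study sites". The usual two-proportion formula is n = [1.96·√(2p̄(1−p̄)) + 0.84·√(p1(1−p1)+p2(1−p2))]² / (p1−p2)², divided by 0.90 for loss.

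- 40% v 25%: 152, so 169 per arm; with continuity correction 165, so 184.
- 45% v 30%: 163, so 182; corrected 176, so 196.
- 50% v 35%: 170, so 189; corrected 183, so 204.

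With 180 evaluable per arm the detectable difference is 13.9 to 14.6 points, or 14.4 to 15.1 with correction. The plan's ability to "detect a risk difference of approximately 15% between the two treatment groups" therefore reproduces. The sample size is not at issue.

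**2. The possible codes for one patient who repeatedly vomits study drug on Day 0.**

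- Section 5.3 and Appendix 2: excluded.
- Section 6.5: quinine, and recoded as complicated malaria. This is compatible with exclusion.
- Appendix 7 and form (4), adverse-event route: ETF, if the event is judged severe. Both include Day 0.
- Danger-sign route: possible ETF on the form, whose window starts on Day 0, but not under Appendix 7, whose window starts on Day 1. Vomiting everything is a listed danger sign (Appendix 8). The parasitaemia condition is met on Day 0, because a positive screening smear is required.
- Section 7.3 (exclusions after enrolment) and the incomplete-outcome boxes on form (4): no entry for vomiting.

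Exclusion and ETF cannot both apply, and the choice decides whether a primary-outcome event is counted.

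**3. Tolerability.** If the patient is excluded, Section 9.2 leaves them out of efficacy, and no stated analysis brings them back. If coded ETF, Section 4.2.3 (items 8 and 9) removes treatment failures from both adverse-event outcomes, and Section 1.0 (secondary outcome 9) removes rescued patients. The event may go uncounted either way.

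**4. Size.** Let v be the share who vomit repeatedly on Day 0 and q the rescue risk in everyone else. Counted as ETF, the arm's risk is v + (1−v)q; excluded, it is q. Counting instead of excluding shifts the risk difference by v1(1−q1) − v2(1−q2). The documents give no v, so the values below are assumptions. I take q1 = 45% and q2 = 30% (middle of the planning range, 15 points apart), so exclusion gives 15.0 points.

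| v1 v v2 | Risks if counted | Difference | Shift |
|---|---|---|---|
| 2% v 1% | 46.1% v 30.7% | 15.4 | +0.4 |
| 4% v 1% | 47.2% v 30.7% | 16.5 | +1.5 |
| 5% v 1% | 47.75% v 30.7% | 17.05 | +2.05 |
| 10% v 2% | 50.5% v 31.4% | 19.1 | +4.1 |
| 2% v 2% | 46.1% v 31.4% | 14.7 | −0.3 |
| 5% v 5% | 47.75% v 33.5% | 14.25 | −0.75 |

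At 4% v 1%, with 4 × 200 = 800 per arm over all sites, 32 and 8 patients would leave.

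If instead the risk with vomiters counted is 45% in both arms, exclusion gives q = (0.45−v)/(1−v). At 5% v 1% this is 42.1% v 44.4%, a spurious 2.3 points; at 10% v 2% it is 38.9% v 43.9%, 5.0 points. Both favour the arm with more vomiting.

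**5. Power.** Removing a further 2%, 5% or 10% from 180 leaves 176, 171 or 162 per arm. Power for 15 points, without correction, is then 82–86%, 80–84% or 78–83%. Loss of numbers is minor.

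**The case against.** Several stronger readings are tempting, and the documents do not support them.

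- A reader might infer that the criterion does remove events unequally by arm, in favour of the less well tolerated regimen. Unequal vomiting is plausible: Section 2.1.1 notes concern about amodiaquine tolerability, and Section 12.2 reports gastrointestinal effects for both regimens. But no rate of repeated Day-0 vomiting is given for either arm. With equal rates the shift is small and runs the other way in the example.
- A reader might see Sections 5.3 and 6.5 as contradictory. One governs participation and the other care and coding, so a patient can be excluded, given quinine and recoded.
- A reader might take more than three vomits to be a severe adverse event or a danger sign. The protocol does not equate them. Appendix 9, Table A puts two to three episodes a day at moderate and defines severe by orthostatic hypotension or intravenous fluids. The ETF route is possible, not certain.
- The difference with vomiters counted is not the true one by default. Whether a switch after vomiting is rescue for symptomatic malaria is a choice the protocol has to make.
- Tolerability data are not ordered to be thrown away: Table 4 schedules adverse-event assessment on Day 0, and Section 8.3 requires a report for moderate or worse events. A safety set may be defined in an analysis plan that is not shown. The clinicians and microscopists who assess outcomes are blinded.

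What stands is that the criterion is applied after dosing, that exclusion and possible ETF are incompatible, that the danger-sign windows differ, and that the adverse-event outcomes stated in the protocol omit failures or rescued patients.

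**Conclusion.** The point holds as a defect of definition with a possible, unquantified bias. An event that depends on treatment is used for selection, and the documents do not settle whether it is an exclusion or a primary-outcome failure. It may therefore be lost from both efficacy and tolerability.

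The effect on the primary risk difference rests wholly on assumed rates: under 1 point if vomiting is equally common in both arms (up to 5%), about 0.4 to 1.5 points at 2% or 4% versus 1%, and about 2 to 4 points at 5% versus 1% to 10% versus 2%. These figures also assume that every such patient would count as a failure. Against a planned difference of about 15 points, this is worth correcting but would not by itself overturn the design. It should be fixed; the case rests on the inconsistent coding rather than on any particular rate.

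**What to change.** - Remove the Day-0 vomiting item from Sections 1.0 and 5.3 and from the screening form as a ground for exclusion from analysis.
- Reconcile Sections 1.0, 5.3, 6.5 and 7.3, Appendix 2, Appendix 7 and clinical record form (4), including its incomplete-outcome boxes, to one definition of the event, one day window and one outcome code.
- If the code is ETF, count it as a failure in the genotype-adjusted outcomes as well, because Section 4.2.1 treats all ETFs as true failures. Censoring these patients there would create a new contradiction.
- Keep every dosed patient in the tolerability and adverse-event analysis, and do not apply to these events the exclusion of rescued patients or treatment failures in Sections 1.0 and 4.2.3.
- Report Day-0 vomiters by arm, and show the efficacy comparison with and without them.

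The cost is wording in the protocol and forms, with no extra visits, and slightly higher observed failure rates if the event counts as failure. No view is taken on how vomiting should be managed clinically.
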